## Abstract

**Background:**

Growing evidence indicates a positive association between physical exercise and both cognitive functions and gaming performance in esports players. However, most existing studies focus on acute or short-term effects and are limited by small sample sizes and a lack of follow-up assessments. Furthermore, comparisons between different exercise modalities remain largely unexplored. Therefore, longitudinal studies comparing optimal exercise protocols and their sustained effects on esports performance are critically needed.

**Objective:**

This study aims to: (1) investigate and compare the long-term effects of 12-week high-intensity interval training (HIIT) and moderate-intensity continuous training (MICT) on various dimensions of esports performance in first-person shooter (FPS) gamers; (2) examine the sustainability of these effects through a 4-week follow-up assessment; and (3) explore the potential associations between physical competence, psychological skills, and gaming performance.

**Methods:**

In this three-arm randomized controlled trial, 195 FPS gamers (aged 18–29) will be randomly assigned to HIIT, MICT, or control groups. Interventions consist of three weekly sessions for 12 weeks (HIIT: 10 × 1-minute high-intensity bouts interspersed with 1-minute active recovery; MICT: 20-minute continuous moderate-intensity exercise). The primary outcome is flicking capacity (a core metric of esports performance). Secondary outcomes include other gaming operational metrics, esports-related psychological skills, body composition, and physical competence. All outcomes will be assessed at baseline, post-intervention (12 weeks), and follow-up (16 weeks).

**Discussion:**

This protocol outlines a standardized longitudinal framework to address the critical lack of evidence-based esports training guidelines. Anticipated findings will further validate the benefits of physical exercise on esports performance, providing essential long-term empirical evidence for integrating optimal exercise modalities into esports training regimens. Furthermore, exploring the associations between physical competence, psychological skills, and operational performance will offer insights into the behavioral pathways of performance enhancement.

**Trial registration:**

ClinicalTrials.gov (NCT07150312). Registered on Aug 29, 2025**.**

## Introduction

Despite its growing prominence, esports lacks a universally standardized definition [1,2], though it is widely characterized as competitive sports facilitated by electronic systems and human-computer interfaces [1,3]. While the industry has achieved substantial global growth [3–6] and mainstream recognition as an official sport [7–9], evidenced by its inclusion in the Asian Games and acknowledgment by the International Olympic Committee, systematic research on esports training and performance lags significantly behind traditional sports [10], highlighting a critical need for scientific evidence to support sustainable competitive development [11–13].

Research in neuroscience, psychology, and sports science suggests that aerobic exercise may enhance cognitive functions relevant to gaming performance, with particular effects on executive control processes. These processes, which include information filtering and rapid decision-making [14–16], are actively involved in video gaming [17,18]. Furthermore, regular physical exercise has been shown to improve stress management and anxiety control, while also enhancing reaction ability and communication skills [19–21], all of which are fundamental components for maintaining optimal performance in competitive esports settings [22,23]. Supporting this connection, studies have identified correlations between cardiorespiratory fitness and reaction time among esports players [24].

Emerging empirical evidence has begun to substantiate the theoretical link between physical activity and esports performance [25–33]. For instance, brief active breaks, such as six-minute walks during gaming sessions, have been documented to enhance executive function in esports players [26]. Additionally, multiple studies have demonstrated the positive effects of pre-game cardiovascular workouts on performance metrics, collectively validating the immediate benefits of physical exercise on esports performance [27,28,34,35].

Nevertheless, current research presents several methodological limitations that warrant attention, including insufficient sample sizes that limit statistical power, predominantly immediate or short-term interventions focusing on acute effects, a lack of follow-up assessments to evaluate the sustainability of effects, and an absence of comparative analyses across different exercise modalities [12,29]. As a training modality with substantial potential for enhancing competitive performance, understanding the long-term adaptations and sustained effects of physical exercise is crucial for developing evidence-based training protocols in esports [12,27,32].

In previous intervention studies, two exercise modalities that have shown potential benefits for improving cognitive function and esports performance are high-intensity interval training (HIIT) and moderate-intensity continuous training (MICT). HIIT involves short bursts of intense exercise followed by rest or low-intensity exercise [36]. This training approach has been associated with significant improvements in cardiorespiratory fitness and has demonstrated unique neurocognitive benefits [37]. Additionally, a single bout of HIIT has been shown to improve esports performance in multiplayer online battle arena (MOBA) gamers [27]. In contrast, MICT involves steady-state aerobic activity maintained at 40–60% of maximum heart rate for extended periods. This approach also has well-established benefits for cognitive function, particularly in domains of sustained attention, working memory, and executive function [38–41]. The mechanisms underlying MICT’s cognitive benefits appear to differ from those of HIIT, involving more gradual but sustained increases in cerebral perfusion, reduced inflammation, and enhanced vagal tone [42–44]. These distinct physiological adaptations suggest that MICT might benefit different aspects of esports performance compared to HIIT, particularly in gaming scenarios requiring prolonged concentration and performance consistency. The differential effects of HIIT versus MICT on brain function have been demonstrated in several studies [45–49]. For example, research shows that while both exercise types can improve cognitive functions, they often do so through different mechanisms and with varying degrees of effectiveness. HIIT tends to show stronger effects on processing speed, while MICT may better enhance sustained attention [48–50]. However, while these physiological and psychological differences between exercise types have been studied in general populations, no research has directly compared these modalities in esports players or measured their effects on actual gaming performance in long-term interventions.

First-person shooters (FPS) hold a prominent position within the esports landscape. These games require players to demonstrate exceptional hand-eye coordination, reaction time, and decision-making skills [51]. Moreover, shooters may be more demanding of players’ reaction time than other esports games, and overall performance is heavily dependent on players’ reaction levels, with reaction time being one of the most essential abilities in FPS [24,51]. These games demand both quick reflexes for moment-to-moment engagements and sustained strategic awareness throughout matches. This combination of performance requirements makes FPS particularly suitable for comparing how different exercise modalities might enhance distinct aspects of gaming performance.

Currently, a standardized or universally agreed-upon method for gauging esports performance has yet to be established. Within the esports arena, it is recognized that performance encompasses not merely physical attributes such as stability of the upper limbs, eye-hand coordination, and manual agility, but also cognitive and psychological dimensions, including resilience to stress, responsiveness, problem-solving skills, and the ability to multitask [22,52]. Existing research predominantly utilizes three measurement approaches: rank-based evaluations [12,53], which provide a holistic view but can be influenced by other confounding factors beyond performance; customized performance tasks simulating specific in-game operations [27,34,54,55], which offer direct insights but often fail to replicate complex competitive environments, thus falling short of assessing holistic, multifaceted performance; and indirect psychological and physiological assessments [26,56,57], which are scientifically robust but may not accurately represent in-game performance [58]. Each method has its strengths and limitations in comprehensively evaluating esports skills, highlighting the need for a more integrated approach to assessment.

Building on our previous 6-week study, which showed no significant improvements in psychological attributes among esports players, we hypothesize that these null findings may stem from insufficient exercise intensity and duration [32]. Given that existing literature consistently identifies psychological skills as fundamental determinants of competitive esports success [12,22,59,60], verifying whether an optimized exercise regimen can effectively enhance these attributes remains an objective of our research. To address the aforementioned limitations in current exercise-esports research and to further advance our previous findings, the current study employs a three-arm randomized controlled trial to compare the effects of a 12-week HIIT and MICT intervention on esports performance and psychological skills, followed by a 4-week follow-up to evaluate the sustainability of these effects. By analyzing the relationships between these performance indicators and physical fitness indicators, we aim to explore the potential underlying mechanisms of different exercise modalities. Ultimately, the findings will offer evidence-based guidance for esports organizations, advancing our understanding of the exercise-psychology-performance relationship in competitive gaming.

## Participants and methods

This research follows the SPIRIT (Standard Protocol Items: Recommendations for Interventional Trials) guidelines (see S1 Checklist), detailing both our current intervention approach and the randomized controlled trial protocol. The entire study is anticipated to take between 18 months to 24 months to complete. Fig 1 outlines the approximate schedule for the study and the estimated duration.

**Fig 1 pone.0357119.g001:**
[figure not shown]
Schedule of enrollment, interventions, and assessments. Note: HIIT: High-Intensity Interval Training; MICT: Moderate-Intensity Continuous Training. -t_1_:pre-allocation/enrollment; t_0_: baseline assessment; t_2_: post-intervention assessment (week 12); t_3_: follow-up assessment (week 16). The symbol “X” indicates that a specific assessment or procedure is performed at that time point. The solid line with dots indicates the continuous 12-week intervention period. For detailed descriptions of the specific instruments and tools used for each assessment variable, please refer to the “Measures” section in the main text.

### Trial registration

The protocol has been registered with ClinicalTrials.gov. The registration number is NCT07150312, and the registration date is 29-08-2025.

### Research objective

This study aims to investigate the long-term effects of HIIT and MICT on esports performance through a 12-week three-arm randomized controlled trial, and to examine the sustainability of these effects with a follow-up assessment conducted 4 weeks after the intervention cessation. Additionally, we seek to compare the differential impacts of these two exercise modalities on various dimensions of esports performance and to explore their associations with changes in body composition and physical competence, thereby providing evidence-based guidance for esports training regimens and enhancing our understanding of the underlying mechanisms by which different exercise approaches influence esports performance.

### Study setting

Measurements and initial parts of the supervised exercise intervention in this study will be conducted in the laboratory of the Department of Sports Science and Physical Education at The Chinese University of Hong Kong. The latter stages of the exercise intervention will be carried out by the participants at their own homes.

### Participants

We will recruit healthy adult FPS gamers of any gender for this study through the university’s mass mail websites and social media platforms such as WeChat groups, and Instagram. Additionally, the QR code for the initial online survey will be displayed at offline esports activities for anyone interested in participating. The age range of participants will be set between 18 and 29 years for two reasons: firstly, this age range represents the primary demographic of current esports participants and professional esports athletes [61,62]; Secondly, setting the age limit at 18 is also in consideration of the regulations of the Chinese National Radio and Television Administration regarding the participation of minors in video games. Under the regulations of the National Radio and Television Administration and the implementation of the Chinese Online Game Fatigue System in games, minors have limited opportunities to engage in esports gaming [63]. Therefore, in compliance with national regulations and for the protection of minors, participants under the age of 18 will not be recruited in this study. As for the determination of esports players, based on previous literature, we will recruit players who have engaged in esports games within the past six months [32,62,64]. In summary, our inclusion and exclusion criteria are as follows:

Inclusion criteria:

18–29 years old;regular FPS players with at least 1 year of FPS gaming experience, who have played FPS games for a minimum of 5 hours per week over the past six months [27];healthy individuals who are capable of physical exercise and tests, assessed and confirmedby the Physical Activity Readiness Questionnaire (PAR-Q) [65];no regular exercise habits (engaging in < 2 structured exercise sessions per week) [66,67];can understand English or Chinese.

Exclusion criteria:

self-reported history of neurological, psychiatric, or medical diseases;having heart disease, hypertension, musculoskeletal injuries, or any other conditions that pose a risk to engaging in physical activitycurrent intake of medications and/or recreational drugs that could affect the central nervous system and/or the ability to learn;a regular user of Aim Lab (used Aim Lab more than once a week in the past six weeks), to prevent baseline bias and potential learning effects, as Aim Lab will be utilized as the primary training and assessment tool in our subsequent intervention.

During the recruitment, we will conduct a preliminary screening of potential candidates through an online questionnaire survey based on our inclusion and exclusion criteria.

### Experimental design

This study is designed as a three-arm randomized controlled trial. Given the limited number of longitudinal studies examining exercise interventions in esports, our sample size estimation was informed by the results of existing acute or short-term exercise studies aimed at enhancing esports performance, alongside preliminary data from our previous research [27,35]. Based on the effects of exercise on esports performance reported in these studies, we conservatively estimated a moderate effect size (d = 0.4) to power our primary outcomes (esports performance). Power analysis conducted via G*Power indicated that a minimum sample of 52 participants per group would be required to detect significant effects with 80% power (α = 0.05). Accounting for an anticipated dropout rate of 20%, 65 participants for each group will be recruited for this study. In total, we will recruit 195 participants, and they will be randomly allocated into three groups (1:1:1): HIIT, MICT, and a control group. To prevent baseline imbalances in variables relevant to gaming performance, a stratified block randomization procedure will be employed. Participants will be stratified into two strata based on their years of FPS gaming experience (e.g., above vs. below the median years of experience of the recruited cohort). Within each stratum, participants will be randomly allocated to the HIIT, MICT, or control group in a 1:1:1 ratio using randomly permuted blocks. The randomization sequence will be generated by an independent researcher using a computer-based random number generator (Research Randomizer) to ensure allocation concealment. The entire allocation process will be conducted by a staff member who will not be participating in the study. In scenarios requiring assessors to utilize measurement tools for evaluating metrics, we engage testers who are completely blind to the participants’ group assignments to conduct the assessments. For metrics tested via computer, our assessors serve merely to facilitate and oversee the process, with the computer’s saved data serving as the definitive record to ensure data objectivity. This approach has been proven reasonable in the past esports performance assessment [27]. The intervention groups will receive a 12-week HIIT or MICT exercise program, while the control group will not receive any intervention. All groups will report their dietary intake, physical activity, sleep patterns, and gaming activity. All participants will undergo a baseline test, followed by an immediate post-test at the end of the 12-week intervention period and a follow-up test 4 weeks after the intervention ends. Fig 2 illustrates the specific experimental procedure.

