The primary outcome will be tested at a two-sided α level of 0.05. For the secondary outcomes, the resulting *p*-values for the group-by-time interaction effects derived from the GEE models will be adjusted using the Benjamini-Hochberg False Discovery Rate (FDR) method. If significant main or interaction effects are detected in the GEE model, simple effect analyses and post-hoc pairwise comparisons will be performed within the GEE framework using estimated marginal means with a Bonferroni adjustment.

Prior to investigating potential associations, we will first test for true inter-individual differences in response to the intervention by comparing the variance of the change between the groups [99]. If true inter-individual variability is confirmed, Pearson’s or Spearman’s rank correlation coefficients will be utilized, as appropriate, to investigate potential associations between esports performance indicators and hand correlates, body composition, and physical competence. To account for multiple testing in these correlation analyses, p-values will be adjusted using the Benjamini-Hochberg FDR method.

All statistical analyses will be conducted using R software (version 4.4.2). A two-sided *p*-value of < 0.05 will be considered statistically significant. To indicate the precision of the estimates, 95% confidence intervals (CIs) will also be calculated and reported.

For the exploratory qualitative component, all semi-structured interviews will be audio-recorded and transcribed verbatim. The transcripts will be analyzed using thematic analysis, facilitated by NVivo 12 software, to identify, analyze, and report recurring themes within the participants’ subjective experiences. Although the sample size is fixed by the intervention design, we will continuously monitor for thematic saturation during this data analysis phase. Rather than formally merging these findings with the quantitative data in a mixed-methods matrix, the qualitative themes will be utilized during the interpretation phase to contextualize the objective performance outcomes. This approach will provide a deeper understanding of the participants’ perspectives and assist in elucidating the potential underlying mechanisms between aerobic exercise and esports performance.

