By comparing multiple exercise modalities against a control condition, this study seeks to identify more effective physical training parameters for enhancing esports performance. The inclusion of follow-up assessments extends beyond immediate effects to examine the duration of exercise-induced benefits after training cessation—a critical consideration for establishing optimal training frequency that allows esports athletes to balance physical training with technical practice time. Furthermore, the larger sample size enables us to draw more reliable conclusions about the differential effects of HIIT and MICT in FPS players, thereby offering more specific data for exercise prescription.

Moreover, several negative health-related consequences have been traditionally associated with excessive screen time and prolonged sedentary behavior in video gamers [100,101]. Excessive sitting time and screen exposure pose potential risks to the health of esports athletes [102,103]. Studies have linked prolonged screen time with lower levels of physical activity and poor cardiovascular health [104,105]. Except for active video games or virtual sports, the majority of video games are typically played in a sedentary position [106]. Should the results of the proposed trial demonstrate that physical exercise effectively enhances esports performance, they could offer a practical rationale for integrating systematic, structured physical training into standard esports regimens. Consequently, while optimizing their competitive outcomes, esports players would concurrently reap the well-established health benefits of regular exercise. This integration would effectively mitigate the health risks associated with prolonged sedentary behavior, exploring a potential dual benefit of enhanced competitive performance and safeguarded occupational health.

The comprehensive approach of this study may contribute empirical data to the ongoing discussion regarding physical training in competitive gaming. These findings could serve as a reference for esports academies and professional teams seeking to incorporate appropriate physical exercise regimens alongside technical and tactical training. By integrating physical exercise into training models, this approach aims to address health concerns that could otherwise undermine the longevity of players’ careers, thereby supporting more sustainable practices within competitive gaming.

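### The inputs printed for the sample size (d = 0.4, alpha 0.05, 52 per group) do not give the stated 80% power for a between-arm comparison unless an unstated within-person correlation of about 0.7 or more is assumed

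*Protocol article*

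**What the plan says.** The sample-size paragraph (Experimental design) takes its effect size from earlier acute or short-term studies and the team's preliminary data: "we conservatively estimated a moderate effect size (d = 0.4) to power our primary outcomes (esports performance"). It then states: "Power analysis conducted via G*Power indicated that a minimum sample of 52 participants per group would be required to detect significant effects with 80% power", at alpha 0.05. The paragraph continues: "Accounting for an anticipated dropout rate of 20%, 65 participants for each group will be recruited for this study". The total follows: "In total, we will recruit 195 participants, and they will be randomly allocated into three groups (1:1:1): HIIT, MICT, and a control group".

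The paragraph does not say which G*Power test was used, which contrast or time point d refers to, which SD scales it, or what within-person correlation was assumed.

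Under Data analysis, the main test is a GEE group-by-time interaction over three arms and three assessments, with an exchangeable working correlation whose value is not given. "The primary outcome will be tested at a two-sided α level of 0.05". If an effect is significant, "post-hoc pairwise comparisons will be performed within the GEE framework using estimated marginal means with a Bonferroni adjustment".

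The discussion (Significance of the study) relies on the sample size for the comparison of the two exercise modes: "the larger sample size enables us to draw more reliable conclusions about the differential effects of HIIT and MICT in FPS players".

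**The concern.** A randomised trial with a control arm is judged on differences between arms. At d = 0.4, two-sided 0.05 and 80% power, a plain two-group comparison needs about twice the stated number per arm. A one-sample or paired t-test with the same inputs returns exactly 52, but it has no control arm and would count any improvement from repeating the Aim Lab task as effect. The printed 80% may therefore not describe the comparisons the trial will report.

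At stake is how the results are read. The 80% figure justifies recruiting 195 people. The article presents its sample size as a strength over earlier, smaller studies and as a basis for conclusions on HIIT versus MICT. If the real power for a pairwise contrast is nearer one half, a non-significant contrast says much less than the stated 80% suggests.

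**Working it through.** **Inputs.** From Experimental design: d = 0.4, alpha 0.05, power 80%, 52 per group, 20% dropout, three equal arms. From Data analysis: two-sided testing, and Bonferroni for pairwise comparisons (three pairs of arms, so 0.05/3 = 0.0167). The baseline to week-12 correlation r is not given; a range is used as an assumption.

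**Step 1: the plan's own figures.** 52/0.8 = 65 and 3 × 65 = 195 both reproduce. For 52 itself:

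- Paired or one-sample t, noncentrality d√n. At n = 51 power is 0.7999. At n = 52 it is 0.4 × √52 = 2.884, power 0.808. The answer is 52.
- Two-sample t, noncentrality d√(n/2): 100 per arm (power 0.7997 at 99, 0.804 at 100). One-sided testing would need 78. Neither gives 52.
- Three-arm one-way F with f = d/2 = 0.20: 244 in total, about 82 per arm.
- Three-group, three-time interaction with f = 0.20 and noncentrality f² × error df: 155 in total, which rounds up to 52 per arm. The default G*Power interaction formula at f = 0.20 and r = 0.5 gives about 53 in total, not per arm.
- Baseline-adjusted two-arm comparison with r = 0.70: 52 per arm.

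So 52 can be reached by more than one route. Of these, only the paired or one-sample test needs no input beyond those printed.

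**Step 2: power of an unadjusted two-arm comparison.** With 52 per arm, the noncentrality is 0.4 × √26 = 2.040 on 102 df.

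| | 52 per arm | 65 per arm | n per arm for 80% |
|---|---|---|---|
| alpha 0.05 | 52.4% | 61.9% | 100 |
| alpha 0.0167 | 35.1% | 44.5% | 133 |

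The 52% also applies, whatever r is, if d is in units of the SD of change. The difference with 80% power at 52 per arm is 0.56 SD, or 0.64 SD at alpha 0.0167. The three-arm one-way F-test with 52 per arm has 54% power if both exercise arms are 0.4 above control, and 42% if one is 0.4 and the other 0.2 above.

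**Step 3: what repeated measures can add.** If d is in outcome-SD units, the standardised effect becomes 0.4/√(2(1 − r)) for change scores and 0.4/√(1 − r²) after baseline adjustment. At r = 0.7 these are 0.516 and 0.560. Power with 52 per arm:

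| r | Change, 0.05 | Adjusted, 0.05 | Change, 0.0167 | Adjusted, 0.0167 |
|---|---|---|---|---|
| 0.3 | 40% | 56% | 24% | 39% |
| 0.5 | 52% | 65% | 35% | 47% |
| 0.7 | 74% | 81% | 58% | 66% |
| 0.8 | 89% | 92% | 78% | 83% |

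Power of 80% at alpha 0.05 needs r of about 0.74 (change) or about 0.70 (adjusted). At alpha 0.0167 it needs about 0.81 or 0.78.

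**Step 4: the planned overall test.** For the 4-df group-by-time Wald test with exchangeable correlation, 52 per arm and one or both exercise arms 0.4 outcome SD better, power is 42%, 57%, 81% and 95% at r = 0.3, 0.5, 0.7 and 0.8. With gains of 0.4 in one arm and 0.2 in the other, it is 44%, 68% and 86% at r = 0.5, 0.7 and 0.8.

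**The case against.** Several stronger readings are tempting, and the article does not support them.

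- **That the authors ran a paired t-test.** The numerical match is exact, but no test is named. A three-by-three interaction under one effect-size convention also gives about 52 per arm and is closer to the planned primary analysis. That route needs a two-group conversion of d to f and a non-default definition of effect size, neither of which is stated. The paired origin remains an inference.
- **That the trial's power is 52%.** That figure belongs to an unadjusted comparison, to d in change-SD units, or to change scores at r = 0.5. The planned GEE uses repeated measures, and at a correlation of about 0.7 or higher the overall test reaches 80%. Since r is not given, neither 52% nor 80% is established.
- **That the trial was meant to have 80% power for each Bonferroni-adjusted pair.** The power statement does not say so; the pairwise comparisons follow a significant model effect. The 35% shows what those contrasts can deliver, not a broken promise.
- **That a null result will be read as no effect.** The article says nothing of the kind and commits to 95% confidence intervals.

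It is also fair that a journal article may leave the choice of G*Power test and the assumed correlation to a fuller document. Their absence alone would be no finding. What stands is that the article prints a power claim, and its printed inputs do not give that power for a comparison between arms.

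**Conclusion.** The concern holds in this conditional form. On the stated inputs, 52 per arm gives about 52% power for an unadjusted two-arm comparison at d = 0.4, and 80% would need 100 per arm. The stated 80% can be right for a between-arm contrast at alpha 0.05 only if d is in outcome-SD units and the baseline to week-12 correlation is at least about 0.70 (baseline-adjusted) or 0.74 (change). Even at r = 0.7, the Bonferroni-adjusted pairwise contrasts have only about 58% (change) to 66% (adjusted). The calculations assume 52 completers per arm, equal variances and approximate normality. The HIIT versus MICT comparison, which the discussion leans on, is not shown to be powered.

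**What to change.** Keep 195 participants and rewrite the sample-size paragraph for the between-arm contrast at week 12. Name the G*Power test, the SD that d refers to and the assumed baseline to week-12 correlation. Then do one of the following:

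- Quote power with 52 per arm over a range of r: for change scores 52%, 74% and 89% at r = 0.5, 0.7 and 0.8; for the baseline-adjusted contrast 65%, 81% and 92%.
- State the difference detectable with 80% power without any gain from correlation: about 0.56 SD, or 0.64 SD with Bonferroni for three pairs.

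Report HIIT versus MICT as an estimate with a 95% CI rather than as a powered comparison. Without correlation gain or multiplicity adjustment, its half-width would be about 1.983 × √(2/52) = 0.39 SD. Soften the sentence on the differential effects of HIIT and MICT under Significance of the study to match.

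The cost is rewording one paragraph and one sentence, with no extra participants. The downside is that the stated power becomes less favourable.
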